### **Methods: validating the prognostic model**

The performance of the model will be evaluated on:

- Model discrimination (ability to differentiate patients who would die within 2 months to those who survived) by calculating the concordance (C)-index (also known as the area under the receiver operator curve), assuming a C-index <0.6 showed poor discrimination [26]
- Model calibration, assessed by plotting the probability of mortality predicted by the model against those observed in the derivation dataset using a calibration plot and the Hosmer-Lemeshow test, assuming a  $p < 0.05$  indicated poor calibration
- Potential clinical usability, practicality and face validity.
- Although the primary outcome measure is mortality risk at 2-months, exploratory analyses will evaluate the performance of the predictive score for deaths at different times by stratifying deaths as early or late (this will be defined based on the distribution of time to death)

Internal validation of the model will be done using bootstrapping of the development dataset to stimulate 100 'resampled' populations of the same size.

External validation of the model will be done using recent (2012 or later) hospital cohorts of HIV-TB patients from the high-prevalence HIV and TB countries in sub-Saharan Africa. Data is from MSF Homa Bay cohort study and LAM RCT clinical trial) is available and planned for external validation.

- Performance of the model will be based on both calibration and discrimination
- Calibration will be investigated by comparing expected mortality outcomes based on the predictive model and actual outcomes and compared using  $\chi^2$  test. The values will also be plotted for comparison, and accompanied by the Hosmer-Lemeshow 'goodness of fit' test

- Discrimination will be tested using both area under the receiver operating curve (the concordance index/C-statistic).
- Mortality risks will be calculated based on the risk score (both either a continuous and/or ordered categorical variable as defined for the derivation cohort)

If performance of the model is sub-optimal, it may be adjusted (either re-calibrated or revised) using the data in the validation dataset. This should improve stability and generalisability of the model.

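### The only numerical calibration criterion, Hosmer-Lemeshow p<0.05 in the derivation data, cannot reveal overfitting, and no calibration slope or intercept is planned internally or externally

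*SAP*

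**What the plan says.** All the calibration text is in the SAP section *Methods: validating the prognostic model*.

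- **Derivation data.** Predicted mortality is set "against those observed in the derivation dataset using a calibration plot and the Hosmer-Lemeshow test", and p<0.05 is taken to have "indicated poor calibration". No other calibration threshold appears in the SAP.
- **Internal validation.** "Internal validation of the model will be done using bootstrapping of the development dataset", with 100 resamples. The text does not say which performance measure the resamples are to correct.
- **External validation.** "Calibration will be investigated by comparing expected mortality outcomes based on the predictive model and actual outcomes", using a chi-square test. "The values will also be plotted for comparison, and accompanied by the Hosmer-Lemeshow 'goodness of fit' test". No threshold is given for either test.
- **Consequence.** "If performance of the model is sub-optimal, it may be adjusted (either re-calibrated or revised) using the data in the validation dataset". The SAP does not define sub-optimal.

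Calibration slope, calibration intercept and an observed/expected ratio with a confidence interval are named nowhere.

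**The concern.** Overfitting makes predicted risks too extreme: too high for high-risk patients and too low for low-risk patients. *Methods: developing the prognostic model* gives it several routes in: univariate associations with the outcome, data-derived categories, fractional polynomials, interaction tests and backward elimination. That section says it aims to avoid overfitting. Yet the one calibration check with a decision rule is made in the data that fitted the model, where overfitting does not show as a departure in mean risk or slope.

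The SAP intends the score for clinical use and for identifying patients who may benefit from added interventions, so the predicted risks themselves matter, not only the ranking. An overfitted score would usually raise no flag under the derivation rule. The external stage would then yield p-values and a plot, but no estimate with a confidence interval on which to base recalibration.

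**Working it through.** The SAP gives no sample size, event count or power for this analysis, so there is no figure of its own to reproduce. The check has an algebraic part and a simulated part.

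**1. Why the apparent slope is 1.** For a maximum-likelihood logistic model with linear predictor L and fitted risk p, the score equations are Σ(y − p) = 0 and Σx(y − p) = 0 for every predictor x. L is a linear combination of the constant and the predictors, so ΣL(y − p) = 0 as well. The recalibration model logit P(y=1) = a + bL has exactly these score equations at a = 0, b = 1. The fitted intercept and slope in the derivation data are therefore 0 and 1, however many noise variables the model holds.

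**2. Derivation test under overfitting.**
- From the SAP: 29% mortality (*Introduction and background*), backward elimination, and at least 10 deaths per candidate (*Methods: developing the prognostic model*).
- Assumed: sample size, number of candidates, 5 true predictors with log odds ratio 0.4 per SD, elimination at p<0.157 (the AIC equivalent), 10 Hosmer-Lemeshow groups, 300 replicates.
- Deaths per candidate = n × 0.29 / k, for example 350 × 0.29 / 10 = 101.5 / 10 ≈ 10.2.

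| Patients | Candidates k | Deaths per candidate | Derivation test rejects | Apparent slope | Mean slope in new data |
|---|---|---|---|---|---|
| 350 | 10 | 10.2 | 4.3% | 1.000 | 0.84 |
| 350 | 20 | 5.1 | 3.0% | 1.000 | 0.72 |
| 350 | 30 | 3.4 | 4.0% | 1.000 | 0.64 |
| 600 | 30 | 5.8 | 6.0% | 1.000 | 0.76 |
| 1,000 | 30 | 9.7 | 4.0% | 1.000 | 0.85 |

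The Monte Carlo standard error near 5% is √(0.05 × 0.95 / 300) = 1.3 percentage points, so every rejection rate is compatible with the nominal 5%. With all 30 candidates kept at 350 patients, the new-data slope fell to 0.50 and the test still rejected only 4.0%.

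**3. What these slopes mean for a patient.** For illustration, take predictions of 60% and 10% and shrink the log odds towards logit(0.29) = −0.895.
- 60% (logit 0.405): slope 0.84 gives −0.895 + 0.84 × 1.301 = 0.197, or 55%. Slope 0.64 gives −0.063, or 48%.
- 10% (logit −2.197): slope 0.84 gives −0.895 − 0.84 × 1.302 = −1.989, or 12%. Slope 0.64 gives −1.729, or 15%.

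**4. External Hosmer-Lemeshow test by cohort size.** Assumed: linear predictor with mean −1 and SD 1, 10 groups, no parameter estimated externally, 1,500 replicates. Cells are percentages rejected at p<0.05.

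| True miscalibration | N=200 | N=400 | N=800 | N=1,600 | N=3,200 |
|---|---|---|---|---|---|
| None | 5.6 | 5.1 | 4.9 | 5.5 | 4.3 |
| Slope 0.8 | 13.5 | 18.4 | 29.9 | 56.0 | 88.9 |
| Slope 0.6 | 36.7 | 61.3 | 91.6 | 99.9 | 100 |
| Intercept +0.2 | 12.7 | 21.1 | 36.3 | 66.2 | 95.3 |

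The same slope of 0.8 would usually go unflagged in a small cohort and would usually be flagged in a large one.

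**The case against.** Much can be said for the plan, and several stronger readings do not hold.

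- **That any model passes the derivation test by construction.** The algebra covers mean calibration and slope only. The test still rejects about 5% by chance and can detect wrong functional form: with an omitted quadratic term it rejected 11-29% at 350 patients and 49-98% at 3,000. If it is applied to the rounded integer score without refitting, slope 1 is not guaranteed either.
- **That p<0.05 also governs external validation.** It is written in the derivation bullet alone. The external tests carry no threshold, and the SAP never says that a non-significant result proves good calibration.
- **That the plan shows neither direction nor size of miscalibration.** Plots accompany the tests in both settings, and expected deaths are compared with actual deaths externally. Direction and rough size will be visible. What is missing is a summary estimate with its uncertainty.
- **That the external result mainly reflects sample size.** At N=400 the rejection rate rises from 5% with no miscalibration to 61% at slope 0.6, and a calibrated model stays near 5% at every size. The dependence on N is ordinary test power. For an overall shift, a one-degree-of-freedom chi-square on total deaths, one reading of the plan, does better than Hosmer-Lemeshow: for 33.7% observed against 29% predicted in 350 patients, about 49-54% against 28%. Its power too depends on N.
- **That the 32 non-outcome rows of Appendix 1 are all candidates, so severe overfitting is expected.** The 10-deaths rule would then require 320 deaths, or 320 / 0.29 ≈ 1,103 patients. With fewer deaths, the list must be cut. In the case nearest the rule at 350 patients the slope is 0.84, a moderate departure. Lower values apply only if outcome-based screening draws on more variables than the rule counts, which the SAP leaves open.

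The plots, bootstrap and external cohorts are real strengths. They do not repair the criterion, because the bootstrap names no calibration measure and the external plan names no estimate.

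**Conclusion.** The point stands in this form: the sole numerical calibration criterion is a test in the derivation data that rejects overfitted models at about its nominal rate (3-6% here), and nothing else in the SAP supplies an optimism-corrected or external calibration estimate with a confidence interval.

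The expected overfitting is moderate if the SAP's events rule binds the variables actually screened (mean slope in new data about 0.84 with 350 patients and 10 candidates). It is larger if it does not (0.72 with 20, 0.64 with 30). These slopes rest on assumed sample sizes, effect sizes and elimination threshold. That the apparent intercept is 0 and the slope 1 needs no such assumption beyond an unpenalised maximum-likelihood fit assessed on its own linear predictor.

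This should be fixed, but it does not invalidate the study: the planned bootstrap and external data already provide what a sound calibration assessment needs.

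**What to change.** 1. Remove Hosmer-Lemeshow p<0.05 as the calibration criterion. Keep the test at most as a supplement.
2. State that the planned bootstrap repeats the whole model-building procedure in each resample (screening, categorisation, transformation, elimination and rounding to points). Apply each resampled model to the original data, and report the mean of those slopes as the optimism-corrected calibration slope.
3. In each external cohort, report the observed/expected ratio or calibration intercept, and the calibration slope, with 95% confidence intervals, beside the planned plot.
4. Say whether calibration is assessed for the regression model, the rounded score or both, and how the score is converted to a predicted risk.
5. Replace the open condition "If performance of the model is sub-optimal" with a decision based, for calibration, on these estimates and their intervals. Any tolerance is for the sponsor to set in advance. An observed/expected ratio of 0.8-1.25 and a slope of 0.8-1.2 would be one example, with no basis in the SAP; a slope of 0.84 would fall inside it.

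The cost is SAP wording and a little more code, with no new data. The reported calibration will probably look less favourable than the apparent figures.

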### **Methods: developing the prognostic model**

A cohort of patients with microbiologically confirmed HIV-TB admitted to hospital in high-prevalence settings in sub-Saharan Africa nested within the STAMP clinical [ref] trial will be used to develop the prognostic model.

- Clinically relevant and pragmatic demographic and clinical variables will be chosen for possible inclusion in the model based upon (1) a priori knowledge from existing studies, (2) based on univariate associations with mortality in development dataset (3) the need for unambiguous, reproducible variables that are available in most clinical settings where the tool may be used.
- In keeping with good practice, a minimum of 10 events (deaths) will be required for each candidate predictor studied.[25]
- Continuous variables (such as CD4 cell count and haemoglobin) will be kept as continuous predictors when practical or converted to ordered categorical variables or dichotomised to simplify the score (based on previously established cut-offs or data-derived categories based on associations with outcomes). Continuous variables will be assessed for non-linearity using fractional polynomials functions, and may need to be transformed in the regression models.
- Univariate associations between demographic and clinical variables and mortality will be tested using  $\chi^2$  and risk ratios with 95% CIs and/or logistic regression.
- A backward elimination stepwise approach to logistic regression modelling will be used to identify candidate predictor variables. Variables will be kept in the model based on p-values using likelihood ratio tests and Akaike information criterion (AIC), aiming to avoid overfitting.
- Further evaluation will include testing for interaction and comparing transformations of predictors where appropriate
- A clinical predictor score will be developed by giving dichotomous variables a value of 0 or 1, and using the regression coefficients from the logistic regression model to calculate the relative contribution of the variable to the risk score. Regression co-efficients will be

rounded to integers and/or scaled and assigned as points to each variable in the final risk score

- The score will be a continuous factor and an ordered categorical factor for simplification, with risk score categories being created based on plotting risk score against observed mortality.

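### The bootstrap is not committed to repeating the outcome-driven selection or to subtracting optimism, so the development C-index may be too high and the predicted risks too extreme

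*SAP*

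**What the plan says.** The SAP section on developing the prognostic model lets the outcome guide most choices:

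- Variables may be picked "based on univariate associations with mortality in development dataset", beside prior knowledge and practicality.
- Continuous variables may be grouped into "data-derived categories based on associations with outcomes". Fractional polynomials, alternative transformations and interactions are also examined.
- "A backward elimination stepwise approach to logistic regression modelling will be used to identify candidate predictor variables", with retention by likelihood ratio p-values and AIC, "aiming to avoid overfitting".
- Points come from the regression coefficients after rounding or scaling. Risk categories are set by plotting the score against observed mortality. No shrinkage step is named.
- One safeguard on model size is given: "a minimum of 10 events (deaths) will be required for each candidate predictor studied".

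The section on validating the model checks calibration against outcomes in the derivation data, with a Hosmer-Lemeshow test. It judges discrimination by the C-index, "assuming a C-index <0.6 showed poor discrimination". Internal validation has a single sentence: "Internal validation of the model will be done using bootstrapping of the development dataset to stimulate 100" resamples of equal size. External validation is planned in two other sources, for both discrimination and calibration. The model may be re-calibrated or revised on those data if it performs poorly.

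**The concern.** A model that is selected and fitted on one dataset looks better there than in new patients. A bootstrap measures this optimism only if each resample goes through the same choices as the original data. Three procedures fit the SAP's sentence:

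1. Score the finished model on the resamples.
2. Refit only the selected variables in each resample and subtract the optimism found.
3. Repeat screening and selection in each resample and subtract the optimism found.

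Only the third accounts for selection. The SAP does not choose between them and does not say that a corrected figure will be reported. The aim of avoiding overfitting is attached to the retention rule alone.

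The planned development calibration check cannot fill the gap. A logistic model fitted by maximum likelihood has a calibration slope of 1 in its own data by construction, so agreement there says little about overfitting.

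Two results are at stake: a development C-index that is too high, and predicted mortality risks that are too high for high-risk patients and too low for low-risk patients.

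**Working it through.** The SAP states no sample size, number of deaths, expected C-index or optimism, so there is no figure to reproduce. The size was illustrated by simulation.

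**Inputs from the SAP.** Mortality is 29% (Introduction). Appendix 1 has 32 predictor rows, not counting the three outcome rows. The rule is ten deaths per candidate, and there are 100 resamples. If all 32 rows count as candidates, the rule needs 32 × 10 = 320 deaths, or 320 / 0.29 ≈ 1,104 patients (843 at 38% mortality, 1,600 at 20%).

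**Assumptions.** Deaths: 100, 150 or 320. Predictors are independent, half of them binary. Four real predictors have coefficient 0.4 in setting A, and six have 0.33 elsewhere. The screen keeps the strongest univariate associations. Backward elimination is at p = 0.157 (equivalent to AIC for one parameter). There are 80 repetitions per setting, and true performance is measured in 20,000 new patients. Cut-off searches, transformations, interactions, imputation and rounding were not simulated.

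**Formulas.** Optimism = mean over resamples of [C of the resample's model in that resample − C of the same model in the original data]. Corrected C = apparent C − optimism. The corrected slope is the mean slope of each resample's model in the original data.

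| Setting | Apparent C | True C | Gap | 1. Finished model | 2. Refit only | 3. Full repeat | True slope |
|---|---|---|---|---|---|---|---|
| A: 10 candidates, 100 deaths | 0.723 | 0.688 | 0.035 | 0.723 | 0.705 | 0.687 | 0.82 |
| B: 32 candidates, 320 deaths | 0.720 | 0.691 | 0.029 | 0.720 | 0.707 | 0.685 | 0.85 |
| C: 32 screened to 15, 150 deaths | 0.736 | 0.677 | 0.059 | 0.736 | 0.712 | 0.676 | 0.71 |
| D: 32 screened to 10, 100 deaths | 0.744 | 0.663 | 0.081 | 0.744 | 0.716 | 0.670 | 0.62 |
| E: 32 candidates, no screen, 100 deaths | 0.749 | 0.661 | 0.088 | 0.748 | 0.718 | 0.660 | 0.58 |

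**Which settings meet the rule.** A and B meet it for every candidate (100/10 and 320/32 = 10). C and D meet it only among screened variables (150/15 and 100/10 = 10; against all 32 rows, 150/32 = 4.7 and 100/32 = 3.1). E meets it only among variables left after elimination (on average 8.7, so 100/8.7 = 11.5). The looser counts cannot be excluded, because the SAP uses the term candidate predictor also for what backward elimination identifies.

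**A different set-up that meets the rule** (eight real predictors, screen at p < 0.20, elimination at p < 0.10). With 11 candidates and 400 patients (0.29 × 400 = 116 deaths; 116/11 = 10.5), the gap was 0.747 − 0.713 = 0.034, slope 0.83. With 32 candidates and 1,104 patients, it was 0.746 − 0.726 = 0.020, slope 0.90.

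**Reading the results.**

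- Procedure 1 removes essentially nothing.
- Procedure 2 removes 0.018/0.035 = 51% (A), 0.013/0.029 = 45% (B), 0.024/0.059 = 41% (C), 0.028/0.081 = 35% (D) and 0.031/0.088 = 35% (E). Its slopes of 0.92, 0.93, 0.88, 0.86 and 0.85 are also too favourable.
- Procedure 3 lands within 0.007 of the true C in every setting. Its slopes are 0.82, 0.82, 0.72, 0.67 and 0.60.
- With 100 resamples the Monte Carlo error of the mean optimism is 0.002 to 0.003.
- A slope of 0.62 means that a patient predicted to lie a distance d from average on the log-odds scale truly lies about 0.62 d from it.

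**The case against.** The strongest reply is that the SAP is silent here, not wrong. A reader might infer that it plans to validate the finished model only and to report an uncorrected C-index. The text does not say so: its sentence is compatible with a full, optimism-corrected bootstrap, which is an ordinary use of the method. That stands, so the fault is a missing commitment.

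Four further replies have weight:

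- **Ten-deaths rule.** Applied to every candidate, it roughly halves the optimism or better. A reader might infer that the 0.6 criterion could easily pass a model without predictive value. With 32 pure-noise candidates and 400 patients, the apparent C does reach 0.6 in about 65% to 68% of runs, but that breaks the rule. When the rule is met the figure is 16% (11 candidates, 400 patients) or 6% (32 candidates, 1,104 patients). The SAP also names predictors already reported, and it does not make passing 0.6 sufficient for adoption.
- **External validation.** A C-index from the two external sources carries no development optimism unless the model is first revised on those data. This limits the harm but does not remove it: revision is allowed, and no validation of a revised model is described.
- **Number of resamples.** A reader might infer that 100 is too few. The Monte Carlo error shows that it is adequate.
- **Shrinkage.** A reader might infer that unshrunk coefficients spoil the score's ranking. One uniform factor cannot change ranking or the C-index, and it leaves scaled points essentially unchanged. It matters for predicted risks.

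**Conclusion.** The concern holds as under-specification with a real consequence. Development is outcome-driven, calibration is checked in the same data, and the bootstrap sentence commits neither to repeating selection nor to correcting for it. Two of the three procedures it permits would leave the development C-index too high, and the predicted risks would be too extreme without shrinkage.

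The optimism to be corrected is about 0.02 to 0.04 in C, with a slope of about 0.8 to 0.9, if the ten-deaths rule covers all candidates. It is about 0.06 to 0.09, with a slope of about 0.6 to 0.7, if the rule is counted only after screening or elimination; the upper end belongs to the settings with 100 deaths. These figures depend on the assumed deaths, effects and independence of predictors, none of which the SAP gives.

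In the settings tabulated above the true C stayed above 0.6 (lowest 0.661). The 0.6 judgement would therefore be at risk mainly for an apparent C between 0.60 and about 0.69 (0.60 + 0.09). The external results are affected only if the model is revised on the external data.

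**What to change.** Amend the internal validation sentence to state that:

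- each resample repeats every outcome-dependent step that can be automated: imputation if used, screening, cut-offs and transformations, interaction tests, elimination and rounding. The resulting score is then evaluated in the original data;
- the optimism-corrected C-index and calibration slope are reported beside the apparent values, and the 0.6 criterion is applied to the corrected C-index;
- the corrected slope is used as a shrinkage factor, with the intercept re-estimated, when the score is converted to predicted mortality risks.

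Steps that rest on judgement and cannot be automated should be named, so that readers know what the correction leaves out. The 100 resamples may stay.

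The cost is SAP wording, computing time and a slightly less favourable development C-index. No new data are needed.

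### If the score is revised on the external validation data, as the SAP allows, the revised score has only apparent performance there and no external validation of its own

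*SAP*

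**What the plan says.** The score is derived in one cohort, "nested within the STAMP clinical [ref] trial will be used to develop the prognostic model" (SAP, Methods: developing the prognostic model). All other statements are in Methods: validating the prognostic model.

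- Internal validation: "Internal validation of the model will be done using bootstrapping of the development dataset", with 100 resamples.
- External validation: "External validation of the model will be done using recent (2012 or later) hospital cohorts of HIV-TB patients". Two sources are named: "Data is from MSF Homa Bay cohort study and LAM RCT clinical trial) is available and planned for external validation".
- Adjustment: "If performance of the model is sub-optimal", then "it may be adjusted (either re-calibrated or revised) using the data in the validation dataset".
- Expected effect: "This should improve stability and generalisability of the model".

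No threshold is attached to the decision to adjust. The general evaluation list has a discrimination criterion, "assuming a C-index <0.6 showed poor discrimination", and treats a Hosmer-Lemeshow p-value below 0.05 as poor calibration, but the latter is tied to the derivation dataset. Neither is linked to adjustment. The next section, Impact of the prognostic model, promises only an outline of future impact studies.

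**The concern.** The decision to adjust depends on the validation result, and the adjustment is then estimated from the same patients. For a revised model, those patients have become training data. Any C-index, calibration plot or Hosmer-Lemeshow test computed there describes apparent performance. The SAP expects better generalisability, but no planned analysis could show it.

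The title and the Aim are to derive and validate a tool for use at admission. If the clause is used for a revision, the tool carried forward is not the tool that was tested. A score applied to individual patients depends on its absolute risks being right, so flattering calibration is the main hazard.

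**Working it through.** The SAP gives no sample size, event count or precision for validation, so it has no figure of its own to reproduce. The check has four parts.

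**1. Which data are left to test a revised model**

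| Source | Planned use | Planned test of a revised model |
|---|---|---|
| STAMP cohort | Development and bootstrap | None; the bootstrap covers the development fit, not a later revision |
| Homa Bay cohort, LAM trial | External validation, then adjustment | None; neither is reserved |
| Further data | None named | None |

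The SAP speaks of a single validation dataset and does not say whether the two sources are pooled or kept apart.

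**2. What each kind of adjustment does**

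Let LP be the linear predictor of the derived model.

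- *Recalibration:* LP′ = a + b·LP. With b > 0 the ranking of patients is the same, so the C-index in the validation data is unchanged and remains a true external value. Only the calibration of LP′ is checked on the data that set a and b.
- *Revision by full refit:* the coefficients maximise the likelihood in the validation data. Fitting logit(p) = a + b·LP_new in those same data returns a = 0 and b = 1 by construction, whatever the truth. Rounding to integer points makes this approximate but does not remove the optimism. The ranking has also been fitted to these patients, so the C-index is apparent.

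**3. Size of the optimism after a full refit**

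The SAP's Introduction gives 29% mortality (95% CI 20–38%). Cohort sizes, predictor counts and effect sizes are assumptions. Each run refits all coefficients by maximum likelihood in a simulated validation set and then evaluates the model in new patients.

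- A: 8 predictors, about 28% mortality, 200 replicates.
- B: 6 binary predictors with 40% prevalence and log odds ratios 0.2–0.7, 29% mortality, 300 replicates.
- C: 8 binary predictors, 29% mortality, 300 replicates.

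| n | Run | Apparent C | C in new patients | Difference | Slope in new patients |
|---|---|---|---|---|---|
| 150 | A | 0.73 | 0.64 | 0.09 | 0.57 |
| 150 | B | 0.692 | 0.619 | 0.073 | 0.61 |
| 150 | C | 0.715 | 0.614 | 0.101 | 0.51 |
| 300 | A | 0.70 | 0.66 | 0.04 | 0.75 |
| 300 | B | 0.674 | 0.633 | 0.041 | 0.76 |
| 300 | C | 0.684 | 0.631 | 0.053 | 0.70 |
| 500 | A | 0.69 | 0.66 | 0.03 | 0.85 |
| 600 | B | 0.667 | 0.641 | 0.026 | 0.85 |
| 600 | C | 0.672 | 0.641 | 0.031 | 0.82 |

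The apparent slope is 1.00 throughout. When setting B is extended to 6 or 10 predictors, mortality of 20%, 29% or 38%, and n from 150 to 600, the C-index optimism runs from 0.018 to 0.135 and the new-patient slope from 0.39 to 0.90.

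The SAP's development rule is at least 10 deaths per candidate predictor. With 8 predictors at 28% mortality, n = 150 gives 150 × 0.28 / 8 = 5.25 deaths per predictor, below that rule. At n = 300 it is 300 × 0.28 / 8 = 10.5, so the rule is met and the optimism is still there.

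*Recalibration for comparison* (8 binary predictors, 28% mortality, development n = 500 with lower baseline risk, 200 replicates): C in the validation set against new patients was 0.644 v 0.639 (n = 150), 0.642 v 0.640 (n = 300) and 0.648 v 0.640 (n = 500). Median new-patient slopes were 0.96, 1.01 and 0.96. In setting C, recalibration left C unchanged and gave mean new-patient slopes of 1.00–1.06.

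**4. The trigger**

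Suppose Hosmer-Lemeshow p < 0.05 in either of two independent cohorts were the trigger, and the test held its nominal size. A perfectly calibrated score would then be adjusted with probability 1 − 0.95² = 0.0975. The SAP does not say that this is its rule; the figure only shows why a rule should be stated.

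**The case against.** Updating a prediction model on data from a new setting is accepted practice, and the clause is optional and conditional. The derived score is evaluated in the external cohorts first, and the SAP applies its risk categories there as set in the derivation cohort. That goes a long way towards fixing the score beforehand. The simulations show the extreme case: every coefficient is re-estimated and the development information is discarded, at assumed sizes. A partial revision would lose less.

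All of this stands, and it rules out three stronger readings that a reader might infer.

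- *That the study ends with no external validation.* The derived score still has one, whatever happens afterwards.
- *That any adjustment inflates the C-index.* Recalibration with a positive slope preserves ranking, so the harm belongs to revision.
- *That the study would present a revised score as externally validated.* The SAP does not say how an adjusted model would be labelled. That is a gap, not a stated false claim.

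The objection does not supply a test, an optimism correction or a label for a revised model. The SAP permits revision on equal terms with recalibration and gives no order of preference.

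**Conclusion.** The point holds for revision and should be fixed. As written, a model revised on the validation dataset would have only apparent performance and no external validation, and the expected gain in generalisability would be untested. For a full refit of 6 to 8 predictors in an assumed 300 patients at 28–29% mortality, the C-index would look about 0.04–0.05 too high and the true calibration slope would be about 0.70–0.76 rather than 1. The optimism shrinks as n grows. These sizes rest on assumed cohort sizes and predictor effects; the direction does not. Recalibration of intercept and slope carries little optimism, with the reservation that its calibration is checked on the data that set it. Nothing follows if the model is not adjusted.

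**What to change.** 1. Lock the score, including its points-to-risk table, before the validation data are opened.
2. Report the locked score's discrimination and calibration in each external cohort as the external validation result, whatever it shows.
3. State in advance what external performance would prompt an update.
4. If updating is wanted, try recalibration before revision. Update in one of the two named cohorts and test the updated score in the other.
5. If that is not feasible, bootstrap-correct the updated model within the data used to update it and label it as updated, not externally validated. The bootstrap corrects for overfitting in those data; it does not show performance in another setting, so the label is still needed.
6. Reword the sentence on stability and generalisability as a hope to be tested, not an expected result.

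The cost is SAP wording. The drawback is that an updated model is tested in one cohort rather than two, so the interval around its performance is wider.
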